## Abstract

**Background:**

Alcohol use disorder (AUD) is characterized by problematic alcohol use accompanied by clinically substantial distress. Patients with AUD frequently experience high relapse rates, and only 1 in 5 remain abstinent 12 months post treatment. Traditional face-to-face relapse prevention therapy (RPT) is a form of cognitive behavioral therapy (CBT) that examines one's situational triggers, maladaptive thought processes, self-efficacy, and motivation. However, access to this treatment is frequently limited due to its high cost, long waitlists, and inaccessibility. A web-based adaptation of RPT (e-RPT) could address these limitations by providing a more cost-effective and accessible delivery method for mental health care in this population.

**Objective:**

This study protocol aims to establish the first academic e-RPT program to address AUD in the general population. The primary objective of this study is to compare the efficacy of e-RPT to face-to-face RPT in decreasing relapse rates. The secondary objective is to assess the effects of e-RPT on quality of life, self-efficacy, resilience, and depressive symptomatology. The tertiary objective is to evaluate the cost-effectiveness of e-RPT compared to face-to-face RPT.

**Methods:**

Adult participants (n=60) with a confirmed diagnosis of AUD will be randomly assigned to receive 10 sessions of e-RPT or face-to-face RPT. e-RPT will consist of 10 predesigned modules and homework with asynchronous, personalized feedback from a therapist. Face-to-face RPT will comprise 10 one-hour face-to-face sessions with a therapist. The predesigned modules and the face-to-face sessions will present the same content and structure. Self-efficacy, resilience, depressive symptomatology, and alcohol consumption will be measured through various questionnaires at baseline, amid treatment, and at the end of treatment.

**Results:**

Participant recruitment is expected to begin in October 2022 through targeted advertisements and physician referrals. Completed data collection and analysis are expected to conclude by October 2023. Outcome data will be assessed using linear and binomial regression (for continuous and categorical outcomes, respectively). Qualitative data will be analyzed using thematic analysis methods.

**Conclusions:**

This study will be the first to examine the effectiveness of e-RPT compared to face-to-face RPT. It is posited that web-based care can present benefits in terms of accessibility and affordability compared to traditional face-to-face psychotherapy.

**Trial Registration:**

ClinicalTrials.gov NCT05579210; https://clinicaltrials.gov/ct2/show/NCT05579210

**International Registered Report Identifier (IRRID):**

PRR1-10.2196/44694

## Introduction

Alcohol use disorder (AUD) is a mental health disorder that affects approximately 3.6% of the global population aged 15 to 64 years [1]. The disorder is highly prevalent and a major contributor to illness and mortality worldwide [2,3]. AUD is characterized by impaired control over alcohol use, leading to physiological dependence and negative psychological, social, and physical consequences [3,4]. The disorder is associated with many physical and psychiatric comorbidities, such as major depressive disorder, generalized anxiety disorder, liver cancer, and hypertension [2,5-7].

The rise in mental health challenges during the COVID-19 pandemic resulted in growing concerns over the health behaviors of individuals with AUD [8]. Stay-at-home orders presented complex relationships between financial issues, low social interaction, and anxiety about the future [9]. Moreover, the disruption to clinical services is believed to have contributed to increased relapse and subsequent negative health outcomes for people with AUD [10]. Kim et al [11] demonstrated that out of 182 participants with previous AUD, 23% increased their consumption during the lockdown. Additionally, 17% of the subjects abstained for an average of 19.5 months before relapsing during lockdown [11].

AUD treatments typically involve abstinence from alcohol due to the high failure rates and risks associated with controlled drinking approaches [12,13]. However, AUD is known as a “relapsing condition,” since patients often relapse following abstinence [14]. Within the AUD framework, a lapse is defined as a single episode of drinking, whereas a relapse involves a return to a pattern of problematic drinking [15]. Stillman et al [16] found that relapse rates in people with AUD are approximately 60% to 80% after 3 months of treatment and 70% to 80% after 12 months post treatment. These rates highlight the importance of integrating relapse prevention into AUD treatment programs. These programs identify personal factors that contribute to relapse and offer helpful strategies to improve coping with cravings, and mood fluctuations, and identify triggers to decrease the rate and severity of relapses [17].

Psychosocial interventions are commonly used to treat AUD, with cognitive behavioral therapy (CBT) being one of the most studied psychological approaches [18,19]. CBT for AUD encourages abstinence in the presence of triggers and cravings by targeting maladaptive thought processes and behaviors [20,21]. This therapeutic approach has demonstrated greater efficacy compared to no treatment or minimal treatment [22]. Relapse prevention therapy (RPT) is a validated CBT treatment for AUD that targets both interpersonal and intrapersonal factors such as motivation and trigger identification. RPT also equips patients with coping strategies to use in situations where alcohol may be available [23-25]. The efficacy of RPT can vary depending on the substance used, personal factors such as income, and comorbid disorders [26,27]. However, despite the effectiveness of this type of therapy, financial issues, accessibility problems, and logistical problems may make it challenging for individuals to receive face-to-face care [28]. Moreover, individuals with AUD frequently experience shame and stigma surrounding their diagnosis, which can reduce treatment seeking in this population [29].

To address some of the issues of accessibility and availability, web-based adaptations of traditional face-to-face psychotherapy, such as internet-based CBT (e-CBT) have flourished in recent years. Web-based psychotherapy offers several advantages, such as not requiring office space, placing lower demands on therapists’ time, improving accessibility, etc [30]. Although the literature has shown comparable effectiveness between web-based psychotherapy and face-to-face psychotherapy in the management of AUD [31], and face-to-face RPT has demonstrated beneficial effects in relapse prevention [12,24], web-based RPT (e-RPT) remains an understudied option for the management of AUD [32].

Therefore, this study proposes the development, study, and implementation of an e-RPT program for the management of AUD. The proposed program could be a viable solution to address the potential accessibility, stigma, and financial issues presented by traditional in-person therapies [32]. Thus, the primary objective of this study is to compare the efficacy of a secure e-RPT program to face-to-face RPT to decrease relapse rates in patients with AUD. Based on the evidence comparing face-to-face and web-based psychotherapies in other disorders, we hypothesize that both face-to-face RPT and e-RPT will have similar effectiveness in AUD symptom management, reducing alcohol consumption, and lowering relapse rates [33,34]. The secondary objective is to assess the effects of online treatment on quality of life, self-efficacy, resilience, and depressive symptomatology. The tertiary objective is to evaluate cost-effectiveness by comparing the amount of time an e-RPT therapist spends with each patient to the therapists administering face-to-face RPT. The results of this study will supplement the available literature and aid in the development of clinical recommendations for the management of AUD.

## Methods

### Study Design and Participants

This is the protocol for a randomized controlled trial studying the efficacy of a novel e-RPT program. Participants (n=60) diagnosed with AUD will be recruited through physician referrals from Kingston Health Sciences Centre, family physicians, other health care providers, and self-referrals within Kingston, Ontario. After providing consent to participate in the study, a Mini International Neuropsychiatric Interview 7.0.2 (MINI) will be conducted to confirm the diagnosis of mild to moderate AUD [35]. The MINI is a diagnostic interview that assesses 17 common mental disorders by following the diagnostic criteria of the *Diagnostic and Statistical Manual of Mental Disorders*, Fifth edition [35]. After the MINI, the Readiness to Change Questionnaire (RCQ) will be administered in an interview format to investigate the individual's desire to change their alcohol consumption [33]. In addition to the RCQ, participants will be asked questions listed in Textbox 1 to capture their history with AUD. Answers to these questions, along with the intake MINI, will be reviewed with the principal investigator (PI) to ensure that the participant meets eligibility criteria and to confirm the AUD diagnosis.

The 6 additional interview questions to establish eligibility.Have you been diagnosed with alcohol use disorder (AUD)?If applicable, when were you diagnosed with AUD?Are you currently enrolled in another relapse prevention program?In the past month, how many times have you had an alcoholic beverage?If applicable, how many drinks did you have on average in those times?If applicable, how many drinks did you have per week on average in the past month?

Participant inclusion criteria are being 18 years or older at the start of the study and having a diagnosis of mild to moderate AUD according to the MINI (2 to 5 MINI AUD symptom criteria) [20], competence to consent and participation, ability to speak and read English, and consistent and reliable access to the internet. Additionally, contemplation about stopping or having stopped consuming alcohol in the past 30 days is required. This will be assessed by the RCQ (participants should be in the contemplation or action stage according to the questionnaire) and by asking them about when they stopped drinking or began considering alcohol cessation [34,35]. Exclusion criteria are acute hypomanic or manic episodes, acute psychosis, other active substance use disorders classified as moderate or severe, active suicidal or homicidal ideation, untreated clinically substantial somatic symptoms or mental disorders, or current enrollment in another relapse prevention program. Additionally, men who consumed more than 4 drinks per day or 14 drinks per week and women who drank 3 drinks per day or 7 drinks per week in the past month will be excluded [36].

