### Procedure

Upon completion of the eligibility assessments, participants will be randomly assigned through a computerized system to one of the 2 groups: e-RPT or face-to-face RPT. Participants will be equally stratified (e-RPT n=30; face-to-face RPT n=30). These treatments will be delivered as an augmentation to treatment as usual (eg, medications, regular physician or clinician visits, referrals, or consultations that are conducted outside of this research study). The e-RPT program will be delivered through the Online Psychotherapy Tool (OPTT), a secure and interactive platform developed by the PI [37]. The face-to-face RPT program will be delivered through videoconference sessions using Microsoft Teams. Participants in the e-RPT and face-to-face groups will also have access to OPTT to access the triage module, the daily drinking diary (Figure 1), and assessment questionnaires.

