### Data Analysis

The data will be initially assessed for outliers, missing, and nonsensical variables. These variables will not be imputed, since they will be handled as missing. Similar studies that involved CBT and e-CBT demonstrated a dropout rate of up to 40% for both conditions once the study concluded [49]. Thus, this study will intentionally oversample the experimental and control groups to account for this dropout rate. Considering the effect size for face-to-face RPT reported by Harada et al [50] (2021) for CBI (effect size=0.65), a significance level of α=.05 and a power of 0.90, a sample size of 60 (30 per arm) would be sufficient to detect substantial changes from our interventions [51]. As this is the first study aiming to establish an e-RPT program for AUD, this sample size calculation relies on data from face-to-face RPT and takes into account the established effectiveness of online psychotherapy compared to face-to-face psychotherapy [30].

The analysis will begin by examining the data for missing, nonsensical, and outlying variables. The data will then be analyzed on a per-protocol basis, excluding missing data, and with intention-to-treat analysis to assess the clinical effects of the program on participants who dropped out prematurely. All calculations will be done using a 2-tailed significance level of α=.05, except for when a Bonferroni correction is needed. The demographic information of program completers and program dropouts will be compared using independent sample *t* tests to identify possible differences. A 2 by 3 repeated measures ANOVA of the primary (daily drinking and relapse) and secondary (SCQ-100, Q-LES-Q-SF, RS-14, CBI, and PHQ-9) outcomes will be conducted to test for the effects of the interventions (e-RPT or face-to-face RPT) throughout the 10-week treatment (0, 5, and 10-week assessment points). Linear regression (for continuous outcomes) and binomial regression analysis (for categorical outcomes) will be used to identify variables associated with outcome measures. Additionally, OPTT will collect usage statistics (ie, number of logins per day, amount of time spent logged in) and compare them to face-to-face metrics (ie, attendance to weekly 1-hour face-to-face sessions) to determine cost and time savings between the 2 programs. All statistical analyses will be conducted using IBM SPSS Statistics for Mac (version 24; IBM Corp).

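### Whether participants have already stopped drinking is recorded before assignment but not used in the stated primary between-arm analysis, which costs some precision

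*Protocol article*

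**What the plan says.** Under Study Design and Participants, the Protocol article requires that "contemplation about stopping or having stopped consuming alcohol in the past 30 days is required". The check is by questionnaire ("participants should be in the contemplation or action stage according to the questionnaire") and by asking when the person stopped or began to consider stopping. The eligibility interview also asks how often and how much the person drank in the past month. An upper limit applies: "men who consumed more than 4 drinks per day or 14 drinks per week" are excluded, with lower limits for women.

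Assignment follows these assessments. Under Procedure, "participants will be randomly assigned through a computerized system to one of the 2 groups: e-RPT or face-to-face RPT", and no stratification factor is named. The sentence "Participants will be equally stratified (e-RPT n=30; face-to-face RPT n=30") gives the size of the arms.

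Data Analysis names the main between-arm model: "A 2 by 3 repeated measures ANOVA of the primary (daily drinking and relapse) and secondary" outcomes, at weeks 0, 5 and 10, with no covariate. Linear and binomial regressions are also planned. Their predictors are not named, and their stated purpose is that they "will be used to identify variables associated with outcome measures".

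**The concern.** For daily drinking, a person who has already stopped starts at or near zero and cannot decrease, while a person still drinking can. Change from week 0 therefore depends on entry status. Having week 0 as a level of the time factor does not remove this, because the arm-by-time term compares changes. If one arm happens to hold more people who have already stopped, part of its time course reflects who was in it.

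For relapse the difficulty is different. Outcome Measures defines relapse as about 4.5 standard drinks on one occasion, or hospitalization because of drinking. The entry limits are below that (more than 4 drinks per day excludes a man; 3 per day excludes a woman), so week-0 relapse should be near zero in everyone. It cannot serve as the baseline adjustment; screening status is what is available.

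The Introduction hypothesizes similar effectiveness. In a trial of this size, avoidable noise in the arm contrast makes a true difference harder to see, and a non-significant result could then be read as similarity.

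**Working it through.** **Inputs from the Protocol article.** 30 per arm; dropout of up to 40%, so 30 × 0.6 = 18 completers per arm; two-sided α = .05; effect size 0.65. The article gives no figure of its own on this point: neither the share abstinent at entry nor the strength of entry status as a predictor. Both are assumed below, over a range.

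**Assumptions.** Share abstinent at entry, q = 0.3 to 0.7. Difference in mean change between the two entry groups, g = 0.5 to 1.0 within-group SD. Dropout unrelated to entry status.

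**1. How often are the arms imbalanced?** Treat the number abstinent in each arm as Binomial(n, q). The SD of the difference in shares is √(2q(1−q)/n). For n = 30 and q = 0.5 this is √(0.5/30) = 0.129. Exact probability of a difference of at least 20 points:

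| n per arm | q = 0.3 or 0.7 | q = 0.5 |
|---|---|---|
| 30 (6 or more people) | 0.120 | 0.155 |
| 18 (4 or more people) | 0.201 | 0.243 |

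**2. What does a 20-point imbalance do to the contrast in change?** Shift = 0.20 × g, which is 0.20 × 0.5 = 0.10 SD to 0.20 × 1.0 = 0.20 SD.

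**3. Error rate of the unadjusted comparison of change** (simulation, q = 0.5, 10,000 trials, no true difference, 30 per arm):

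| g | all randomizations | only those with an imbalance of 20 points or more |
|---|---|---|
| 0 | 4.8% | 5.5% |
| 0.5 | 5.1% | 5.9% |
| 1.0 | 5.0% | 12.2% |

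The last column rests on about 0.155 × 10,000 = 1,550 trials, so its Monte Carlo standard error near 6% is √(0.059 × 0.941/1,550) = 0.6 points. The 5.9% is barely distinguishable from 5%; the 12.2% clearly is.

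**4. What does adjustment gain?** Share of variance explained by status: R² = g²q(1−q)/(1 + g²q(1−q)). Standard error ratio: √(1−R²). At q = 0.5:
- g = 0.5: R² = 0.0625/1.0625 = 0.059; ratio 0.970, a 3% reduction.
- g = 1.0: R² = 0.25/1.25 = 0.20; ratio 0.894, an 11% reduction.

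At q = 0.3 or 0.7, q(1−q) = 0.21. The ratios are then 1/√1.0525 = 0.975 and 1/√1.21 = 0.909, so the reductions are about 2.5% and 9%.

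**5. Power for a true difference of 0.65 within-group SD, 30 per arm** (simulation, 5,000 trials). With g = 0.5, power rises from 66.8% unadjusted to 68.5% adjusted. With g = 1.0, it rises from 60.4% to 69.7%. As a check, g = 0 gives 70.1% unadjusted against 69.7% from the noncentral t. That this falls short of the stated 90% is a separate matter and is not relied on here.

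**The case against.** **A condensed article may leave strata and covariates to the full protocol or analysis plan, and the unnamed regressions could include entry status.** This stands in part: nobody can say from the article that allocation is unstratified, only that no factor is named. But the article does state the primary model and its factors, and it gives the regressions a different purpose from estimating an adjusted arm effect. Adding a variable already in hand improves a choice that the article has made.

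**An unadjusted analysis of a randomized trial is valid.** This stands. A reader might infer that chance imbalance makes the primary test wrong. Step 3 shows that it does not: error is about 5% over all randomizations, and the distortion is conditional on an unlucky draw.

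**The strength of the factor is unknown.** This stands. A reader might call entry status a strong prognostic factor, but the article gives no figure, and the drinking limits narrow the gap between the groups. A reader might also assume a baseline correlation of 0.5 and value adjustment at 60/(1 − 0.25) = 80 participants' worth. For a 50:50 factor that needs a difference of about 1.15 SD. Under the range above the equivalent is 60 × 1.0625 ≈ 64 to 60 × 1.25 = 75.

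**The argument about opposite directions does not carry over to relapse.** This stands, since week-0 relapse is near zero in both groups; what remains there is that entry status probably predicts later relapse. Even an assumed 30-point gap in relapse risk turns a 20-point imbalance into 0.20 × 30 = 6 points. At 45% relapse the standard error is √(2 × 0.45 × 0.55/30) = 12.8 points. For drinking too, the article does not say what period the week-0 value covers, so someone who stopped recently may not start at exactly zero.

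**Readiness stage is not abstinence.** This also stands. The questionnaire addresses the wish to change, so it should not stand in for whether the person has stopped.

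**Conclusion.** The point holds as a modest, nearly free improvement. Entry status is known before assignment, is likely prognostic for the two primary outcomes, and is absent from the stated primary between-arm model. The cost is precision (a standard error about 3–11% larger than it need be, at q = 0.5) and conditional bias of 0.10–0.20 SD when the arms differ by 20 points. Such a difference has probability 12–16% at 30 per arm and 20–24% at 18. All of this depends on the assumed 30–70% abstinent and 0.5–1.0 SD difference in change. At the low end the gain is small.

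The documents do not support reading this as an inflated overall error rate or an invalid design. Nor do they show the mechanism for the secondary scales.

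**What to change.** - In the primary between-arm models, prespecify one entry-status covariate: abstinent or drinking at screening, defined from the reported stop date rather than from readiness stage. In a repeated measures model, enter it with its interaction with time; a main effect alone leaves the arm-by-time contrast unadjusted.
- For the drinking outcome, add past-month drinks per week from the eligibility interview. Use this recall as a covariate, not as the week-0 level of the diary outcome.
- For relapse, keep to entry status alone. With about 36 completers, a binary model with several covariates may be unstable.
- If randomization has not started, also stratify the computerized allocation by entry status.
- In any case, replace *stratified* under Procedure with *allocated 1:1*.

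No new data are needed. The price is one or two degrees of freedom in a model for a single post-treatment value; an interaction over three time points takes two per covariate.

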### Procedure

Upon completion of the eligibility assessments, participants will be randomly assigned through a computerized system to one of the 2 groups: e-RPT or face-to-face RPT. Participants will be equally stratified (e-RPT n=30; face-to-face RPT n=30). These treatments will be delivered as an augmentation to treatment as usual (eg, medications, regular physician or clinician visits, referrals, or consultations that are conducted outside of this research study). The e-RPT program will be delivered through the Online Psychotherapy Tool (OPTT), a secure and interactive platform developed by the PI [37]. The face-to-face RPT program will be delivered through videoconference sessions using Microsoft Teams. Participants in the e-RPT and face-to-face groups will also have access to OPTT to access the triage module, the daily drinking diary (Figure 1), and assessment questionnaires.

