### e-RPT

Participants in the e-RPT group will receive 10 predesigned online modules per week on the OPTT platform. Each module consists of approximately 30 slides and should have an estimated completion time of 45 minutes. At the end of each module, participants will be assigned homework to be completed before their next module is assigned. The therapists will submit personalized feedback by using session-specific therapy feedback templates. These structured templates standardize the quality of feedback across different patients and therapists. In previous studies, therapists have been able to effectively use these templates to prepare feedback in approximately 15-20 minutes [30].

This e-RPT program will focus on teaching essential cognitive and behavioral skills such as identifying maladaptive thought processes, increasing engagement in day-to-day activities, and developing strategies to reduce alcohol consumption. The content of the sessions is outlined in Table 1.

**Table 1 table1:** The program outline and session summary for the 10-week web-based and face-to-face relapse prevention program.

Session number	Session subject
1: Understanding addiction	Introduces relapse prevention and what to expect from the course. The session explains what addiction is, including the symptoms, signs, consequences, and different types of addiction. Participants will create a SMART goal that they will try to achieve throughout the program. They will also share their personal experiences with addiction.
2: Exploring and strengthening your motivation	Focuses on the 5 stages of motivation and the role of motivation in relapse prevention. Helpful techniques are discussed to help them reflect on and boost motivation throughout their recovery journey. Participants will create a pros and cons list about stopping alcohol use and reflect on different aspects of their ability to stop using alcohol.
3: Triggers	Describes what triggers are and how to recognize them, including both internal and external triggers. This session also provides strategies to handle triggers through avoidance and careful planning. Participants will learn to identify their triggers and to be prepared for them if encountered.

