### Outcome Measures

The primary objective of this study will be to determine if e-RPT has similar effectiveness to face-to-face RPT at reducing alcohol consumption and preventing relapses. This study defines relapse as either the consumption of at least 2.5 oz. of pure ethanol, which is around 4 and a half standard drinks (Canadian guidelines for standard drinks: 12 oz of beer with 5% ethanol, 12 oz of cider with 5% ethanol, 5 oz of wine with 12% ethanol, and 1.5 oz of spirits with 40% ethanol) [41,42] on one occasion or hospitalization because of alcohol drinking [43]. Therefore, to determine the effectiveness of this program, daily alcohol consumption will be recorded in a drinking diary accessible through OPTT. This diary will ask the participants to report how many drinks they consumed on each day of the week, where they had those drinks, with whom, and if their alcohol consumption resulted in hospitalization (Figure 1).

The study will also determine whether e-RPT and face-to-face RPT have a beneficial effect on self-efficacy, quality of life, resiliency, coping behaviors, and depressive symptomatology. These metrics will be assessed through the following scales: Situational Confidence Questionnaire (SCQ-100) [44], 14-item Resilience Scale (RS-14) [45], Coping Behaviors Inventory (CBI) [46], Patient Health Questionnaire (PHQ-9) [47], and Quality of Life Enjoyment and Satisfaction Questionnaire—Short Form (Q-LES-Q-SF) [48]. These assessment scales will be completed at study entry (baseline), amid the program (week 5), and post treatment (week 10). After the treatment period, we will conduct follow-up assessments with all our outcome measures at 3, 6, and 12 months. The amount of time that e-RPT therapists spend writing feedback compared to the 1-hour face-to-face session will be used as a measure of therapists’ time efficiency and will be tracked on the OPTT platform.

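### Diary access is equal, but only e-RPT brings participants back to the diary's platform for therapy; unequal diary completion could create or hide a relapse difference during the 10 weeks

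*Protocol article*

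**What the plan says.** All references are to the protocol article.

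- **Delivery (Procedure).** For the experimental arm, "The e-RPT program will be delivered through the Online Psychotherapy Tool (OPTT), a secure and interactive platform developed by the PI". For the comparator, "The face-to-face RPT program will be delivered through videoconference sessions using Microsoft Teams".
- **Diary access (Procedure; Triage Module).** "Participants in the e-RPT and face-to-face groups will also have access to OPTT to access the triage module, the daily drinking diary", together with the questionnaires. Both arms complete the same triage module, which introduces the diary.
- **Reason to return to OPTT (e-RPT; Face-to-Face RPT).** In the e-RPT arm, "participants will be assigned homework to be completed before their next module is assigned". In the face-to-face arm homework is gone through in the live session, and no recurring therapy task on OPTT is described.
- **Source of the outcome (Outcome Measures).** "daily alcohol consumption will be recorded in a drinking diary accessible through OPTT". The diary also carries the question on hospitalization. No second source for drinking is named. On layout: "This diary will ask the participants to report how many drinks they consumed on each day of the week".
- **Relapse definition (Outcome Measures).** At least 2.5 oz of pure ethanol "on one occasion or hospitalization because of alcohol drinking".
- **Analysis (Data Analysis).** Daily drinking and relapse are the primary outcomes, tested by a 2 by 3 repeated measures ANOVA at weeks 0, 5 and 10. On missing, outlying or nonsensical values: "These variables will not be imputed, since they will be handled as missing". Nothing in the stated model refers to the number of diary days recorded.

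**The concern.** In one arm, recording the outcome shares a platform with receiving treatment. In the other it is a separate errand. An e-RPT participant who is active in therapy is already on OPTT; a face-to-face participant who is equally active in therapy has to go there for the diary. The link could also work the other way, since an e-RPT participant who gives up the modules loses the main reason to log in, while a live therapist may remind the participant about the diary.

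Relapse is an any-event outcome: one qualifying day is enough, so the chance of observing it rises with the number of days observed. If completion differs by arm, observed relapse differs even when the therapies are equally effective and missed days are unrelated to drinking. Randomisation does not protect against this, because the difference arises after allocation. Recruiting extra participants for dropout does not protect against it either. The trial's hypothesis is similar effectiveness, so a recording gap that masks a real difference is as troublesome as one that invents a difference.

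**Working it through.** The article gives no figure on this point to reproduce: no completion rates and no daily relapse risk. What follows is an illustration on stated assumptions.

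**1. Basic illustration**

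Inputs: 70 days (the 10-week phase); the same true daily relapse risk h in both arms (assumed); a share p of days recorded (assumed); days missing at random. Observed any-relapse is 1 − (1 − h·p)^70.

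With h = 1%:
- true relapse: 1 − 0.99^70 = 50.5%
- 90% recorded: 1 − 0.991^70 = 46.9%
- 80% recorded: 1 − 0.992^70 = 43.0%
- 60% recorded: 1 − 0.994^70 = 34.4%

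The spurious gap is 46.9 − 34.4 = 12.5 points for 90% versus 60%, and 43.0 − 34.4 = 8.6 points for 80% versus 60%. Over h from 0.5% to 2% and recording gaps of 20 to 30 points, the range is about 5 to 17 points. With equal completion the gap is 0.

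**2. Risk taken from the article's own background figure**

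The Introduction cites relapse of 60% to 80% at 3 months. Taking 3 months as 90 days, the daily risk is 1 − (1 − R)^(1/90): 1.01% for R = 0.60 and 1.77% for R = 0.80. Observed relapse at completion c is 1 − (1 − daily risk)^(70c).

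| Completion | R = 0.60 | R = 0.80 |
|---|---|---|
| 90% vs 80% | 3.9 points | 4.3 points |
| 90% vs 70% | 8.1 points | 9.2 points |
| 90% vs 60% | 12.6 points (47.3% vs 34.8%) | 14.8 points (67.6% vs 52.8%) |
| 90% vs 50% | 17.4 points | 21.1 points |

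In a simple two-proportion comparison (not the planned ANOVA) with 30 per arm, 90% versus 60% completion raises the chance of a significant result in that direction from 2.5% to about 16% (R = 0.60) or 21% (R = 0.80), with no true difference.

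**3. What makes the gap smaller**

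*Between-person variation.* Averaging the formula in step 1 over gamma-distributed risk (shape 0.5, mean 1% or 2% per day) gives 7.2 or 7.8 points for 90% versus 60%, and about 5 to 9 points over recording gaps of 20 to 30 points.

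*Several qualifying days per relapser.* If 60% relapse and each relapser has k qualifying days, the observed proportion is 0.60 × [1 − (1 − c)^k], so the gap for 90% versus 60% is 0.60 × (0.4^k − 0.1^k):
- k = 1: 18 points
- k = 2: 9 points
- k = 3: about 4 points
- k = 5: 0.6 points

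**4. Daily drinking**

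The mean number of drinks per recorded day is not shifted by days missing at random, however many are missing. It is biased only if unrecorded days differ from recorded ones. The detection argument therefore applies to relapse, not to both primary outcomes.

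**The case against.** The strongest reply is that the design treats the arms alike where it matters. Both have the same diary on the same platform and the same introduction to it, and reliable internet access is an entry criterion for everyone. The number of days on which a relapse can be recorded is therefore identical. This stands: only the days actually completed can differ, and a reader who infers unequal access goes further than the text.

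It is also tempting to infer that e-RPT participants who stop the modules will stop recording, or that face-to-face participants will neglect the diary. The article describes no reminders, therapist checks or completion rates in either arm, so neither is established. Contact is weekly in both arms, and a diary set out by day of the week may let one visit fill in several days. The diary figure, which might settle this, is not available. Loss of independent single days is thus a modelling convenience.

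The article also does not say how diary days are summarised into relapse at weeks 0, 5 and 10. An any-relapse proportion over 70 days is one reading, and a fuller protocol or analysis plan may define it and allow for unrecorded days. Applying the non-imputation sentence to single diary days is likewise an inference.

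Finally, follow-up at 3, 6 and 12 months falls after therapy has ended on both platforms, so the asymmetry concerns the 10-week phase.

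These points remove any claim of error or of known bias. They do not remove the asymmetry in what brings participants back to OPTT, or the dependence of a one-occasion outcome on days observed.

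**Conclusion.** The point holds as a foreseeable risk to the relapse comparison in the 10-week phase, and as a cheap improvement. No statement in the article is wrong or contradictory here.

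The asymmetry, the single stated source for drinking, the one-occasion definition and the absence of any allowance for days recorded are all in the text. The size is not. The 12.5-point gap rests on assumed completion of 90% versus 60%, a uniform 1% daily risk and days missing at random. It becomes about 5 to 9 points with strong between-person variation (recording gaps of 20 to 30 points), falls below 1 point if relapsers have about five qualifying days, and is nil if completion is equal. The direction is unknown: fuller e-RPT diaries would make e-RPT look worse on relapse, and fuller face-to-face diaries would do the reverse.

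A reader might conclude that both primary outcomes are biased. That is not supported: mean drinks per recorded day is affected only if unrecorded days differ from recorded ones.

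**What to change.** - **Procedure and Outcome Measures:** state that both arms receive the same automated diary prompt on the same calendar, independent of module release and session attendance.
- **Data Analysis:** analyse the number of relapse days with the log of recorded diary days as an offset, or analyse time to first relapse with unrecorded days not counted as at risk.
- **Reporting:** give diary days completed by arm beside the primary result, so that readers can judge whether unequal recording occurred.

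The cost is a platform reminder setting and a few sentences of text. Prompting has to be in place while the diary is being kept, since unrecorded days cannot be recovered reliably afterwards. There are two drawbacks. Equal prompting adds a little self-monitoring to both arms. And analysing per recorded day corrects for how much was recorded, not for participants choosing not to record drinking days.
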